### Preoperative examination

Preoperative examination of patients will include blood biochemistry, alpha-fetoprotein assay, chest x-ray, percutaneous ultrasonography, computed tomography (CT) scan, and hepatic angiography in selected patients. Liver function will be assessed by Child-Pugh grading and the indocyanine green clearance test.

### Acquisition of samples

Blood samples: Two blood samples will be obtained from each patient after induction of general anesthesia through a central venous catheter, which is routinely placed just before surgery. EDTA (not heparin) will be used as an anticoagulant for blood samples. Follow-up blood samples will be collected every 6 months postoperatively.

Tissue samples: Paracarcinomatous tissue and cancer tissue will be harvested from the resected liver specimen at the time of resection. Paracarcinomatous tissue should be harvested 1 cm from the tumor margin. All tumors will be pathologically confirmed to be HCC.

Each tissue sample will be divided into two parts, one of which will be placed in liquid nitrogen and the other in 10% formalin. Serial 4-μm sections from each specimen will be stained with hematoxylin and eosin to determine clinicopathological features such as venous invasion, capsule formation, Edmondson’s grade, and cirrhotic nodules.

### Sample size calculation and data analysis plan

The sample size of this trial was calculated using data from our previous experience and from the published literature. There are currently no data from randomized controlled trials showing the recurrence rate of HCC after hepatectomy without the Pringle maneuver. Most studies used the Pringle maneuver. This trial plans to have equal numbers of control and experimental subjects, and a 36-month follow-up period. The median survival time after the treatment that the control group will receive has been reported to be 26 months [24,44-50]. We anticipate a10-month difference in the median recurrence-free survival time between the experimental and control groups. If median survival times in the control and experimental groups are 26 months and 36 months, respectively, we will need to include 249 experimental subjects and 249 control subjects to be able to reject the null hypothesis that the experimental and control survival curves are equal with a probability (power) of 0.800. The Type I error probability associated with this test of the null hypothesis is 0.05.

Data for primary and secondary outcome measures will be analyzed using the SPSS statistical software package (SPSS UK Ltd., Woking, U.K.). Analysis will include standard descriptive statistics, Student’s t tests, correlation and regression, and two-way (group x time) repeated measures ANOVA to examine differences between the groups over time. Survival analysis will be performed. Statistical significance will be set at p < 0.05and all tests will be two-tailed. Subgroup stratified analysis will be performed according to tumor size, tumor encapsulation, Edmondson’s grade, HBV load, ischemic time, blood loss, and transfusion. The intention-to-treat analysis will be used for the patients whose portal triad clamping was changed due to safety reasons.

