**Figure 1 F1:**
[figure not shown]
**Detailed flow chart of the clinical trial.** Eligible patients from five centers will be enrolled, and randomly divided into an experimental group and a control group by permuted-blocks randomization. Each patient will be followed up for 3 years after their primary operation.

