### Experimental group (group a, non-Pringle group)

The liver will be mobilized from the retroperitoneum and the peripheral ligament. Anatomical liver resection is preferable. If anatomical resection is not possible, a surgical margin of more than 2 cm should be achieved, except if the location of tumor nodes makes this impossible (e.g., close to the inferior vena cava or portal vein).The resection method and surgical margin will be recorded for analysis. The liver parenchyma can be resected according to the surgeon’s preference and local standards (CUSA, Tissue-link.). The Pringle maneuver will not be used, and hepatic inflow and outflow will be maintained. For safety, the surgeon may use the Pringle maneuver if major bleeding occurs.

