### Follow-up

Patients who have completed the interventions will be included in the standard follow-up program. Follow-up visits will be at 1, 3, 6, 9, and 12 months and then every 6 months until 3 years after their operation. Each visit will include physical examination, tumor marker tests, liver function tests, chest x-ray, and ultrasound examination. In addition, enhanced CT scans of thorax and abdomen will be performed at 3, 6, 12, 18, 24, 32, and36 months postoperatively. Additional investigations including 18 F-fluorodexyglucose positron emission tomography scan, magnetic resonance imaging, or digital subtraction angiography will be scheduled as required to investigate possible tumor recurrence. At each visit, a follow-up evaluation form will be completed. If tumor recurs, the patient will be hospitalized and treated according to the clinical situation.

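### The 249 per arm for 0.800 power fits follow-up of 36 to 45 months, but each patient stops at 36 months, where power is about 0.77 before any crossover or loss

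*Protocol article*

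**What the plan says.** The section on sample size and data analysis takes the control median from the literature ("The median survival time after the treatment that the control group will receive has been reported to be 26 months") and assumes a 10-month gain: "If median survival times in the control and experimental groups are 26 months and 36 months, respectively". It concludes that "we will need to include 249 experimental subjects and 249 control subjects to be able to reject the null hypothesis". The null here is equality of the two arms' curves, and the power is put at 0.800. On the error rate it says "The Type I error probability associated with this test of the null hypothesis is 0.05", and it makes all tests two-sided. It mentions 36 months of follow-up without saying whether this is counted from each operation or from the last enrolment.

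Other sections answer that question. The Figure 1 legend says "Each patient will be followed up for 3 years after their primary operation". The Follow-up section sets visits in the first year and "then every 6 months until 3 years after their operation", with the last CT at 36 months. The section on trial duration gives 9 months of recruitment and 36 months of follow-up. The Endpoints section closes the study when the last patient completes 3 years, yet places the final evaluation of the endpoints 1 year after the last enrolment.

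On crossover, the experimental-group section states "For safety, the surgeon may use the Pringle maneuver if major bleeding occurs". The control-group section also lets the surgeon change technique, and such patients stay in the intention-to-treat analysis.

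**The concern.** In a time-to-event design, power depends on the number of events, and events depend on how long patients are observed. A calculation that credits early patients with up to 45 months counts events that a 36-month schedule will not record. If that is what happened here, the 0.800 belongs to a different design from the one described.

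The trial questions a routine surgical manoeuvre, and a non-significant result would be used in that debate, so the power quoted beside it should be that of the trial as run. Crossover under intention-to-treat and loss to follow-up would each lower power further, and nothing in the sample size text shows that either was allowed for.

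**Working it through.** **Inputs.** Medians 26 and 36 months, power 0.80, two-sided 0.05 and 249 per arm (sample size section); 9 months of recruitment (trial duration section); 36 months per patient (Figure 1 legend and Follow-up section). Assumptions of this check: exponential survival, uniform accrual, a log-rank test, no loss and no crossover.

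**Events needed.** The hazard ratio is 26/36 = 0.722, and ln(36/26) = 0.3254. Required events = 4 × (1.960 + 0.8416)² / 0.3254² = 4 × 7.849 / 0.1059 = 296.5, about 296.

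**Reproducing 249.** Per arm, n = 2 × 7.849 / (0.1059 × p), where p is the event probability at the mean median of 31 months.

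- 9 months of accrual plus 36 months after it closes: p = 0.595, n = 249.1. This is the protocol's figure.
- 36 months for every patient: p = 1 − exp(−ln 2 × 36/31) = 0.553, n = 268.1.

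**Other formulas, n per arm:**

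| Formula | Follow-up 36 to 45 months | 36 months each |
|---|---|---|
| Schoenfeld | 247.4 | 265.9 |
| Mean-median log hazard ratio | 249.1 | 268.1 |
| Lachin-Foulkes | 250.3 | 269.1 |
| Freedman | 251.6 | 270.4 |

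Two proportions at 36 months gives 282 (299 with continuity correction). One-sided Schoenfeld with 36 months each gives about 210. None of the calculations with 36 months each comes within 3% of 249.

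**Power at 249 per arm, 36 months each.** Event probabilities are 1 − exp(−ln 2 × 36/26) = 0.617 (control) and 0.500 (experimental). Expected events = 249 × (0.617 + 0.500) = 278.1. Power = Φ(½√278.1 × 0.3254 − 1.960) = Φ(0.754) = 0.774. The mean-median formula gives 0.770, and a log-rank simulation of 20,000 trials gave 0.773.

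**Power at 249 per arm, 36 to 45 months.** Event probabilities are 0.659 and 0.541, giving 298.9 events and power of 0.800 to 0.803 (simulation 0.800).

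**Final evaluation 1 year after last enrolment, read literally.** Follow-up would be 12 to 21 months. Event probabilities are 0.354 and 0.271, giving 155.8 events and power of 0.528 (0.521 by the mean-median formula and by simulation).

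**Crossover and loss, illustration only.** The 249 equals the formula result without inflation, so it holds no allowance for either. Suppose a share of non-Pringle patients are clamped and take the control hazard, with 36 months each. At an assumed 5% power is about 0.73. At an assumed 10% it is about 0.68 from the expected log-rank statistic and 0.69 by simulation. Suppose instead that patients lost contribute no events and there is no crossover: an assumed 5% loss gives 0.75 and an assumed 10% gives 0.73.

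**The case against.** The strongest reply is that nothing was miscalculated. The figure of 249 follows from medians, recruitment time and follow-up time that are all printed in the article, under the usual model of accrual plus follow-up, and the Endpoints section does end the study at the last patient's 3-year point. That stands: the calculation is correct for a common cut-off and does not match the per-patient schedule. The study end date does not remove the mismatch, because no visit or scan is planned beyond 3 years for patients enrolled earlier.

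The reply continues that the effect is small. That also stands. The loss is about 2.5 points of power. At 80% power, 278 events detect an experimental median of about 36.4 months instead of 36.0, and the 10-month gain is itself a guess, since the article says no randomised data exist. The Abstract calls 498 a minimum, which permits more patients but commits to none. A null result should in any case be read from its confidence interval.

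A reader might infer that true power is 0.73, 0.68 or lower because of crossover. The documents do not support this as a finding. They give no rate of crossover or loss, they also allow technique changes in the control arm, which the one-way illustration ignores, and a condensed article may leave such allowances to the full protocol. Keeping crossed patients in their randomised arm is correct.

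A reader might equally take 0.53 as the real power. The text on final evaluation conflicts with the 3-year follow-up stated elsewhere, so this is a contradiction to resolve and not an established design feature.

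The recruitment figures do not close the gap. At the anticipated 50 patients a month, 9 months give 450, and 498 would take about 10. With 10 months of accrual plus 36 the mean-median formula gives 247.3 per arm, which still relies on follow-up beyond 36 months.

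**Conclusion.** The point holds in a limited form. The stated 0.800 belongs to a design with 36 to 45 months of follow-up. With 36 months per patient, as the Figure 1 legend and the Follow-up section require, 249 per arm gives about 278 events against about 296 needed, and power of about 0.77; 80% would need roughly 266 to 271 per arm. This rests on exponential survival, the protocol's own medians and a two-sided log-rank test, with no crossover or loss.

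Taken alone, the mismatch is minor to moderate. Values below 0.77 for crossover or loss are sensitivity figures on assumed rates. The timing of the final evaluation matters more for power, and it must be settled before any power figure is restated.

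**What to change.** First reconcile the Endpoints section's final evaluation at 1 year after last enrolment with the 3-year follow-up stated elsewhere. Then choose one of two changes.

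1. **Restate the power.** In the sample size section, say that follow-up is 36 months per patient and that 249 per arm gives about 278 events and power of about 0.77, before crossover and loss. The only cost is a slightly less favourable figure.
2. **Use a common cut-off.** Follow all patients to one date 36 months after the last randomisation, which gives about 299 events and power of 0.80 before crossover and loss. This fits the recruitment and follow-up periods already planned and needs no extra patients. It costs the earliest patients up to 9 more months of routine follow-up, or about 10 if recruitment runs at 50 a month, and the Follow-up and Figure 1 texts must change to match.

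The second option works only for a log-rank comparison of whole curves. The Study design section frames the primary objective as disease-free survival rates at 1, 2 and 3 years, and observation after month 36 adds nothing to a 3-year rate. For that comparison, two proportions with 249 per arm give power of about 0.75, whatever the cut-off. The section should therefore name the test to which the power refers.

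Any crossover or loss figures should appear as labelled sensitivity calculations and not as planning values, unless the sponsor can support a rate.

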### Study design

This study is funded by the National Major Science and Technology Project of China on the prevention and treatment of infectious diseases, for human immunodeficiency virus and HBV [2008ZX10002-026]. This clinical trial is a registered [NCT00725335], prospective, intraoperatively randomized multicenter trial of patients undergoing curative resection for HCC. The patients will be stratified by center and allocated to groups by a permuted-blocks randomization protocol. The primary objective of this study is to compare the disease free-survival rates at 1, 2, and 3 years postoperatively between the two groups. We hypothesize that the long-term prognosis of patients who have undergone curative resection will be worse in the control group (Pringle maneuver) than in the experimental group (non-Pringle maneuver).

The detailed study design is shown in Figure1.

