### Randomization, stratification, and blinding

This is a randomized multicenter study. After giving informed consent and being enrolled in the study, patients will be randomized into different groups in the operating room after surgical exploration. The permuted-blocks randomization protocol will comprise five separate randomization lists, one for each participating hospital, and will be centrally managed by the Clinical Trial Center of the lead hospital, the Third Military Medical University. When an eligible case is enrolled, the Clinical Trial Center will be called and a randomization number will be assigned according to the designated list. Because there are two groups in this trial, the block sizes will be 4, 6, and 8 and will be randomly assigned. Patients will be stratified by site and randomized in a ratio of 1:1 into the two groups. Patients and outcome assessors will be blinded to achieve a minimum bias.

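### Repeated-measures ANOVA suits the three-year laboratory series poorly, and the stated analysis of recurrence does not carry over centre stratification or adjust for baseline prognosis

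*Protocol article*

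**What the plan says.** Under Sample size calculation and data analysis plan, the protocol article lists descriptive statistics, t tests, correlation and regression, and "two-way (group x time) repeated measures ANOVA to examine differences between the groups over time". It adds that survival methods will be used, without naming a test or model. The ANOVA is not tied to an outcome. The repeated continuous data are laboratory values: blood taken at induction of anaesthesia and six-monthly after surgery (Acquisition of samples), and tumour markers and liver function at visits up to three years (Follow-up).

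On allocation, Study design says "The patients will be stratified by center and allocated to groups by a permuted-blocks randomization protocol", and Randomization, stratification, and blinding describes "five separate randomization lists, one for each participating hospital". The analysis section mentions neither centre nor a covariate-adjusted treatment comparison. It plans subgroup analyses by seven factors. The Discussion says that known prognostic factors are dealt with through the eligibility criteria and these subgroups.

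**The concern.** Classical group-by-time ANOVA needs a complete row for each patient. Over three years after liver cancer resection, rows will be broken by death, by care for recurrence and by missed visits. The patients who remain are fewer and are selected partly by outcome, possibly to a different degree in each arm. The laboratory comparison over time would then lose precision and could be distorted.

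For recurrence the issue is efficiency. Randomising within centres and then analysing without centre discards part of the design. Subgroup analyses do not adjust the overall treatment effect, so they recover none of the power that strong baseline prognosis can cost an unadjusted log-rank test. Three of the listed subgroup factors (ischaemic time, blood loss, transfusion) also arise after randomisation and could not serve as adjustment covariates.

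**Working it through.** **1. The plan's sample size.** Inputs from the sample size section: "If median survival times in the control and experimental groups are 26 months and 36 months, respectively"; "survival curves are equal with a probability (power) of 0.800"; "The Type I error probability associated with this test of the null hypothesis is 0.05"; "all tests will be two-tailed"; "we will need to include 249 experimental subjects and 249 control subjects". Recruitment of 9 months is from the section on trial duration.

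- Exponential hazard ratio: 26/36 = 0.722; ln(0.722) = −0.3254.
- Schoenfeld events: 4 × (1.960 + 0.842)² / 0.3254² ≈ 296.5, so 297.
- Event probability with uniform accrual over 9 months plus 36 months of follow-up, at the averaged median of 31 months (λ = ln 2/31 = 0.02236): 1 − (e^(−36λ) − e^(−45λ))/(9λ) = 0.595.
- Patients per arm: 296.5/(2 × 0.595) ≈ 249.1, matching the stated 249.
- With the mean of the two arm probabilities (0.600), 498 patients give 299 events: √299/2 × 0.3254 − 1.96 = 0.85, so power is 0.80.

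The match needs the 9-month accrual. A cut-off at exactly 36 months for everyone gives 265 to 268 per arm, or power 0.77 at 498. That is a question of follow-up, separate from this point.

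**2. Share of patients left in the ANOVA.** Six-monthly sampling over three years gives six postoperative samples. The document states no missingness rate, so these are scenarios.

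- 5% missing independently at each sample: 0.95⁶ = 0.735, about 366 of 498.
- 10% missing: 0.90⁶ = 0.531, about 265 of 498.
- Series ends only at death, with assumed three-year survival of 60% to 90% and 0% to 5% missing per sample: from 0.60 × 0.735 = 0.44 to 0.90.
- Series ends at recurrence (not stated): 0.5^(36/26) = 0.383 with Pringle and 0.5^(36/36) = 0.50 without, before any missed visits.

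**3. What complete-case selection does.** In an illustrative simulation the series ended at recurrence and the hazard depended on the observed marker (150 trials per setting). A true slope difference of −0.10 was estimated as −0.085 to −0.091 in completers and −0.096 to −0.103 by a likelihood-based mixed model. With no true difference, completer bias was at most about 0.01. The SD of the completer estimate was roughly 10% to 20% larger.

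**4. Power for recurrence.** This used 2000 simulated trials per setting, 498 patients, five equal centres and a conditional hazard ratio of 0.722. Centre variation and covariate strength are assumed, because the document gives neither.

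| Setting | Unadjusted log-rank | Centre-stratified log-rank | Cox, score and centre |
|---|---|---|---|
| No centre variation, no score | 0.810 | 0.813 | 0.816 |
| Centre log-hazard SD 0.2 | 0.800 | 0.800 | 0.802 |
| Centre log-hazard SD 0.4 | 0.758 | 0.772 | 0.782 |
| Score log-HR 0.3 per SD | 0.764 | 0.761 | 0.794 |
| Score log-HR 0.5 per SD | 0.736 | 0.732 | 0.802 |
| Score log-HR 0.8 per SD | 0.632 | 0.628 | 0.798 |

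In the first three rows, centre stratification gains 0 to about 1.5 points. In the last three, adjustment gains about 3, 7 and 17 points over the unadjusted test. Simulated type I error was 0.048 and 0.040 unadjusted and 0.056 and 0.058 adjusted (Monte Carlo SE about 0.005), so the adjusted gains may be slightly flattered.

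**The case against.** The strongest reply is that much of this is silence. The document is a condensed article, and strata and covariates of a survival model are usually settled in a full protocol or SAP. The planned survival analysis and regression exclude neither. A reader might infer that the trial ignores centre and baseline prognosis. The document supports only that no stated analysis names centre and that the described route for prognostic factors is eligibility and subgroups. An unadjusted randomised comparison is valid. This reply does not cover the ANOVA, which is a named method.

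A reader might also infer that the trial is underpowered. It does not follow. The medians of 26 and 36 months describe whole arms. If they hold, the unadjusted test has the planned 0.80, and adjustment would add to it. The lower unadjusted figures in the table arise because 0.722 was taken as a conditional effect beside an assumed score.

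Nor do the documents support the inference that the ANOVA threatens the primary result. Recurrence is a time-to-event outcome, and no outcome listed under Endpoints is a repeated continuous measure. The ANOVA plausibly serves the blood tests named in the aims. Recurrence is also not the same as missing data, since nothing says that sampling stops then.

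Finally, a mixed model does not abolish survivor bias. It is valid under missing at random, informative dropout can remain, and values after death are undefined.

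**Conclusion.** The point holds as a modest, inexpensive improvement. The named ANOVA is a poor choice for a three-year laboratory series. Under assumed independent missingness of 5% or 10% per sample it would keep 74% or 53% of patients. The 38% against 50% split applies only if sampling ends at recurrence. The simulated attenuation of the slope difference, about 0.01 to 0.015 on a true 0.10, is small and depends on the model chosen.

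For recurrence, the stated analysis does not reflect the centre-stratified design and describes no adjusted treatment comparison. Centre stratification is worth little power by itself; its main merit is that the analysis then follows the randomisation. Covariate adjustment may matter more, but the 3 to 17 points depend on the assumed covariate strength. The sample size and planned power need no correction on this account.

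**What to change.** - **Serial laboratory outcomes:** replace the repeated-measures ANOVA with a linear mixed model containing arm, visit, arm-by-visit interaction, baseline value and centre, using all available visits. State the missing-at-random assumption, whether sampling continues after recurrence, and how values after death are handled (for example, comparing values while alive and reporting them beside overall survival).
- **Recurrence:** name a log-rank test and Cox model stratified by centre. Add a supporting Cox model, also stratified by centre, with a few prespecified preoperative factors such as tumour size, number of nodules and HBV load. Keep ischaemic time, blood loss and transfusion out of it.
- **t tests:** reserve them for uncensored continuous outcomes.

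The cost is a change of analysis wording, made before outcome data are examined. It needs no extra patients or visits. The named software can fit these models, and the suggested covariates are factors the protocol already names for subgroup analysis or as prognostic.

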## Background

Hepatocellular carcinoma (HCC) is one of the most common cancers worldwide, and has been ranked the second leading cancer killer in China since the 1990s [1]. Chronic hepatitis B virus (HBV) infection is the most common etiology in China [2].

Curative resection remains the best choice of HCC therapeutic strategies to date, but local tumor recurrence and remote metastasis unfortunately occur in many patients who have undergone surgery. Although there have been great advances in the diagnosis and treatment of HCC, the long-term prognosis is still unsatisfactory due to a high incidence of tumor recurrence, ranging from 50% to 60% [3-6]. The reason for this high recurrence rate is not entirely clear. Locoregional tumor recurrence with concomitant hepatic decompensation is the main cause of death. It is suggested that further strategies may be needed for the prevention and treatment of early and late recurrence [7].

The Pringle maneuver is a classical surgical technique widely used during hepatectomy since its advent in 1908[8]. During hepatic resection, severe bleeding represents a major life-threatening risk [9,10]. The Pringle maneuver (continuous or intermittent clamping of the hepatic artery and portal vein) is routinely used to reduce intraoperative bleeding [11,12]. It seems inevitable that maneuver causes ischemia-reperfusion (I/R) injury, resulting in complex metabolic [13,14], immunological [15], and microvascular [16-18] changes, which together might contribute to hepatocellular damage and dysfunction[13,19]. Over the past century, the effects of the Pringle maneuver have been widely discussed [8,20-32]. From the reported data, we know that the technique can significantly reduce blood loss during hepatectomy, meanwhile damaging the liver remnant through the I/R injury. Interestingly, the effects of the Pringle maneuver on the prognosis of oncology patients and on the behavior of tumor cells have not been specifically discussed. It remains unknown whether tumor recurrence and metastasis can be influenced by this surgical stress.

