### Endpoints

The primary trial endpoint will be tumor recurrence diagnosed by enhanced CT scan or serum alpha-fetoprotein level. Secondary objectives are to examine overall survival, blood loss, duration of operation, requirement for blood transfusion, length of hospital stay, and morbidity rate. The formal end of the study will be at the end of the 3-year follow-up period of the last patient to be enrolled. All these parameters will be recorded prospectively as part of the study protocol. Final evaluation of the primary and secondary endpoints of the study will be performed 1 year after enrollment of the last patient.

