## Discussion

Even though short-term outcomes of the Pringle maneuver have been investigated, its effects on tumor recurrence and metastasis have not been discussed. This trial will focus on the effects of the I/R injury caused by the Pringle maneuver on the long-term prognosis of primary HCC patients with HBV infection.

Previous experimental studies have demonstrated that tumor recurrence could be increased by I/R injury to the liver remnant, and that the tumor cell might become more aggressive [33,35]. If this occurs in the clinical setting, use of the Pringle maneuver must be re-evaluated, because it has been widely performed in the past to avoid massive blood loss during hepatic resection. The Pringle maneuver may cause additional I/R injury besides that caused by the hepatic resection itself, which will affect tumor cells and the liver remnant.

With advances in surgical techniques and perioperative management, portal triad clamping is not necessary for every hepatectomy, and it may be important to further discuss its use. We hypothesize that the prognosis of patients with primary HCC might be worsened by use of the Pringle maneuver during hepatectomy. If this is true, this routine surgical technique should be revised or even avoided during hepatectomy, especially in HCC patients. We all know that it can take time for theories based on animal experiments to have an effect on clinical practice. In some cases, the final outcome may be affected by multiple clinical factors. For this trial, reported data indicate that these factors mainly include the hepatitis virus DNA load, surgical margins, microvascular thrombosis, tumor size, number of tumor nodules, microvascular invasion, tumor capsule formation, blood loss, and blood transfusion. We take all these factors into account in our inclusion and exclusion criteria and subgroup analysis. Whatever the results of this randomized controlled trial, we will gain important information about the long-term effects of the Pringle maneuver.

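### Ischemic time, blood loss and transfusion are planned as subgroup factors, but all three arise after randomisation and depend on the arm, so arm comparisons within their strata are not randomised comparisons

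*Protocol article*

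**What the plan says.** Under Sample size calculation and data analysis plan, the protocol article states: "Subgroup stratified analysis will be performed according to tumor size, tumor encapsulation, Edmondson’s grade, HBV load, ischemic time, blood loss, and transfusion". All seven factors stand in one list, which ends with "HBV load, ischemic time, blood loss, and transfusion", and nothing marks the last three as different in kind. The Discussion names factors that may influence the outcome, blood loss and transfusion among them, and adds: "We take all these factors into account in our inclusion and exclusion criteria and subgroup analysis".

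Four other places bear on these three factors:

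- Randomization, stratification, and blinding: "patients will be randomized into different groups in the operating room after surgical exploration".
- Experimental group: "The Pringle maneuver will not be used, and hepatic inflow and outflow will be maintained", with one exception: "For safety, the surgeon may use the Pringle maneuver if major bleeding occurs". The Pringle maneuver section has 15-minute occlusions in the control arm, repeated according to need.
- Background: "the technique can significantly reduce blood loss during hepatectomy".
- Endpoints: "Secondary objectives are to examine overall survival, blood loss, duration of operation, requirement for blood transfusion".

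**The concern.** A subgroup analysis of a treatment effect keeps the protection of randomisation only if the subgroups are formed from features that the treatment cannot change. Once patients are sorted by something the treatment influences, the two arms within a stratum are different selections of patients.

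That matters here because the Discussion offers the subgroup analysis as a way of taking prognostic factors into account. A reader will want to know whether avoiding clamping still helps once bleeding is considered, and tables by blood loss or transfusion would seem to answer that. They could show a difference where none exists, and could show it in every stratum, which would look like consistent confirmation.

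**Working it through.** **1. When each factor is determined.** Allocation follows exploration and precedes transection. Clamping time, blood loss during resection and the transfusion that follows all come later. Tumour size, encapsulation and Edmondson's grade are tumour features that clamping does not determine, even though some are read from the resected specimen. HBV load is a patient characteristic, provided the preoperative value is used.

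**2. Whether each depends on the arm.**

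- Ischemic time: zero in the non-Pringle arm unless the patient is clamped for major bleeding, and above zero by design in the Pringle arm. A zero stratum holds essentially only non-Pringle patients. A stratum above zero compares Pringle patients with the non-Pringle patients who were clamped because they bled. This follows from the text without any figure.
- Blood loss: the Background says clamping lowers it.
- Transfusion: the article does not state an effect of clamping on it. That it follows from bleeding is an inference.

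**3. The plan's own figure.** The 249 per arm reproduces. HR = 26/36 = 0.722. Events = 4 × (1.96 + 0.84)² / (ln 0.722)² ≈ 297. With 9 months of accrual and 36 months of follow-up, the exponential event probabilities are 0.6595 and 0.5409, so n = 297 / (0.6595 + 0.5409) ≈ 248 per arm. None of this involves the subgroup factors.

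**4. Possible size for blood loss.** The documents give no inputs, so every strength below is an assumption. In the model, log blood loss = a × (non-Pringle) + b × U + N(0, 1), where U is a standard normal case-difficulty factor. The recurrence hazard is (ln 2 / 26) × exp(g × U), with censoring at 36 months and no true effect of the arm. Patients are split at the median blood loss. HRs are non-Pringle versus Pringle.

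| a, b, g | Overall HR | Low half | High half |
|---|---|---|---|
| 0.5, 0.5, 0.3 | 1.00 | 0.96 | 0.96 |
| 0.5, 1, 0.5 | 1.01 | 0.93 | 0.93 |
| 1, 1, 0.5 | 1.00 | 0.86 | 0.85 |
| 0, 1, 0.5 (technique does not affect bleeding) | 1.01 | 1.00 | 1.01 |
| 1, 1, 0 (difficulty not prognostic) | 0.99 | 0.99 | 0.99 |

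In the third row, 63.8% of non-Pringle but only 36.2% of Pringle patients fall in the high half. At equal blood loss, the non-Pringle patients are on average the easier cases, hence HRs below 1 in both halves.

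A variant has b = 0.6, residual SD 0.5 and blood loss 33% or 45% lower with clamping (a = 0.4 or 0.6; 1 − exp(−0.4) = 0.33, 1 − exp(−0.6) = 0.45). It gives stratum HRs of about 0.84 to 0.89 when difficulty carries a recurrence HR of 1.65 per SD, about 0.91 to 0.94 at 1.28 per SD, and about 0.94 to 1.00 at 1.11 per SD. Stronger inputs reach about 0.81. Transfusion and ischemic time were not simulated.

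**5. On the scale of this trial.** Half of 498 is 249 patients. At about 60% with an event this is about 150 events, so the SE of the log HR ≈ 2/√150 = 0.16. A bias to 0.96 or 0.93 is 0.25 or 0.44 SE (ln 0.96 = −0.041, ln 0.93 = −0.073), and the two-sided false-positive rate in one stratum becomes about 6% or 7% instead of 5%. A bias to 0.89 or 0.84 is 0.71 or 1.07 SE (ln 0.89 = −0.117, ln 0.84 = −0.174), and the rate becomes about 11% or 19%.

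**The case against.** The best counter-argument concerns ischemic time. The article does not say in so many words that the arms will be compared within levels of it. The Pringle maneuver section has occlusion times recorded for analysis, so the authors may intend an analysis by duration among clamped patients only. That reading is possible, but the subgroup sentence carries no such limit and lists ischemic time with factors that serve for comparing the arms. Followed as written, it gives an invalid contrast.

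Three further objections stand and limit the point:

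- A reader might infer that every planned subgroup is biased. The documents do not support that: the problem is confined to strata of these three factors.
- A reader might infer that the bias is known to favour the trial's hypothesis. That needs a factor driving both bleeding and recurrence. The article calls blood loss prognostic but does not say why. Under the same assumption, the comparison among clamped patients could even go the other way, since the non-Pringle patients in it are those who bled heavily.
- With about 150 events per blood-loss half, a bias of 0.93 to 0.96 would hardly be visible against sampling error.

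It cannot be said that the matter is left to an unseen analysis plan, because the article itself names these variables as subgroup factors.

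**Conclusion.** The point holds for the three factors. That they arise after randomisation and that ischemic time and blood loss depend on the arm rests on the protocol's own text; for transfusion, dependence on the arm follows from its link to bleeding. For ischemic time the difficulty is the near absence of any between-arm contrast, which is worse than bias.

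For blood loss the bias is possible and not quantified by the documents. With no true effect, stratum HRs of about 0.81 to 1.00 follow from the assumed strengths. The distortion disappears if the technique does not affect bleeding, which contradicts the Background, or if case difficulty does not affect recurrence. The low end reflects the inputs tried and is not a bound.

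It would be wrong to conclude that the trial's main result is compromised. The overall intention-to-treat comparison does not condition on these variables, and the sample size does not use them. This is a flaw in secondary analyses that should be corrected.

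**What to change.** Remove ischemic time, blood loss and transfusion from the treatment-effect subgroups, and keep tumour size, encapsulation, Edmondson's grade and HBV load. Analyse blood loss and transfusion as outcomes by arm, as the Endpoints section already provides. If their role in any effect on recurrence is of interest, add a mediation analysis labelled exploratory, with its assumptions stated. Use ischemic time only in an exposure-response analysis within the Pringle arm, labelled non-randomised, because the number of occlusion cycles depends on how the operation goes. Adjust the Discussion sentence on how these factors are taken into account.

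The cost is a change of analysis wording. Data collection, sample size and patient care stay as they are, and the sponsor gives up three subgroup tables that have no valid causal reading.
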